##### Acceptability

Measures of acceptability and usability of the program will be assessed at postintervention (6-week postbaseline). *The usability of the program* will be assessed using the 10-item System Usability Scale [68]. Items are rated on a 5-point Likert scale ranging from 1 (*strongly disagree*) to 5 (*strongly agree*). The scores for each item are converted to a new number, ranging from 0 to 4. A total score is then computed by summing the converted item scores and multiplying this by 2.5, giving a range of 0 to 100. Higher values denote greater usability and higher satisfaction with the program. Cut-off scores using a *school grade analogue* have recently been suggested for interpreting the scores (F=0-51.7; D=51.8-62.6; C=62.7-72.5; B=72.6-78.8; and A=78.9-100), with a score over 68 being considered above average [69]. *Satisfaction* with the program will be measured by Client Satisfaction Questionnaire-8 [70]. Items are rated on a 4-point Likert scale from 1 to 4, with total scores ranging from 8 to 32. Higher scores indicate greater client satisfaction. Acceptability will also be assessed by 13 acceptability items (eg, how user-friendly, simple to use, logical, and engaging the tasks were), rated using a 5-point Likert scale from 0 (*not at all*) to 4 (*very*). The survey will also contain several open-ended questions about the most or least helpful and enjoyable features of the program. To determine *which intervention delivery model is preferred*, participants in the active intervention groups will complete four user experience questions after completing each of the *Re-train Your Brain* sessions. The four items will assess their motivation while training, how much they enjoyed the training, how much they liked the delivery format, and whether they found the training simple and user-friendly, using a 5-point Likert scale (from 0 *not at all* to 4 *extremely*).

#### Secondary Outcome Measures

##### Overview

The following measures will be assessed at baseline, postintervention, and 3 months postbaseline (a more detailed description and interpretation of scores are given in Multimedia Appendix 1).

##### Cognitive Biases

*Alcohol approach biases* will be assessed using the Alcohol Approach Task [13]. Participants are instructed to pull or push a computer mouse (in place of a joystick, which is typically used in laboratory-based studies) in response to an irrelevant feature of images (ie, the orientation as portrait or landscape) shown on a computer screen while ignoring the content of the pictures. Two categories of pictures are used: 20 alcoholic beverages and 20 color- and shape-matched nonalcoholic beverages. Each picture appears one by one in both landscape and portrait formats in a quasi-random order (maximum 3 consecutive pictures of the same category or format). Contingent upon a pull or push movement, the picture zooms in (becomes larger on the screen to generate the subjective experience of an approach behavior) or zooms out (becomes smaller on the screen to give a sense of avoidance behavior). A correct response is followed by feedback, as indicated by a green ✓on the screen, whereas an incorrect response is followed with error feedback, as indicated by a red X. The task begins with 5 practice trials showing empty rectangular frames in a landscape or portrait format. Format movement assignments are counterbalanced (half of the participants pull pictures that came in landscape format and push portrait pictures, and half of the participants received the opposite instruction). The images have been selected to represent the beverage type and brands most commonly consumed by this population, as documented in a recent acceptability study [51]. Each image is repeated twice, for a total of 80 trials.

*Social anxiety interpretation biases* will be measured using the Interpretation Recognition Task [22,71]. The Interpretation Recognition Task contains two parts: an encoding phase and a recognition test phase. During the encoding phase, participants are asked to read a set of 10 ambiguous social scenarios presented on a computer screen. Each scenario consists of a title and three short sentences that are ambiguous in terms of valence. In the final sentence, a word fragment is presented. After reading a scenario, participants are asked to complete the word fragment as quickly as possible by pressing the spacebar when they know what the word is. They then press the key corresponding to the first missing letter. Next, the participant is asked to answer yes or no to a question that measures comprehension of the story, also followed by feedback (ie, *correct* or *wrong*). An example of the encoding phase is provided as follows:

(Title): *The evening class.*

(Scenario): You’ve just started going to an evening class. The instructor asks a question and no one in the group volunteers an answer, so he looks directly at you. You answer the question, aware of how your voice must sound to the...

(Word fragment): oth-rs

(Correct word): others

(Comprehension question): Have you been going to the evening class for a long time?

(Response): No

(Feedback): ✓ Correct answer

In the recognition test phase, participants are presented with the identifying titles of each ambiguous scenario, together with four interpretations of each of the scenarios, presented one at a time. Participants are asked to rate each summary statement independently for their similarity in meaning to the original scenario on a 4-point Likert scale from 1 (*very different in meaning*) to 4 (*very similar in meaning*). The four summary statements always contain one valid, positively valanced interpretation (positive target); one valid, negatively valanced interpretation (negative target); one positively valanced statement that was not a possible interpretation of the original scenario in that it did not correspond to the previously presented ambiguity (positive foil); and one negatively valanced statement that was not a possible interpretation of the original scenario (negative foil). Foils are included to assess any wider priming effects, indicating a potential response bias for endorsing any information of a certain emotional valence. Examples of the summary statements that would be provided for the aforementioned scenario are shown as follows:

Positive target: You answer the question, aware of others listening attentively.Negative target: You answer the question, aware of how unsteady your voice sounds.Positive foil: You answer the question and then realize what a good answer it is.Negative foil: You answer the question but realize that you have made a mistake.

*Interpretation and expectancy biases for co-occurring social anxiety and alcohol use* will be assessed by the self-report Comorbid Social Anxiety and Alcohol Interpretation Bias task [59]. Participants are presented with a set of eight ambiguous social scenarios, followed by three possible explanations for the situation. Participants will rate the degree to which each of the explanations would likely be true if they were in that situation (0 *not at all likely* to 8 *extremely*).

##### Alcohol Use

*Alcohol consumption* (average drinks per day) and frequency of binge drinking days (>5 standard drinks per drinking day) in the past month will be assessed through a computerized version of the Timeline Followback Procedure [60-62]. *Hazardous alcohol use* will be assessed using the 10-item Alcohol Use Disorder Identification Test [54]. *Severity of alcohol dependence* will be assessed using the 20-item Severity of Alcohol Dependence Questionnaire [63]. *Alcohol cravings* will be assessed using the 12-item Severity of Alcohol Craving Questionnaire–Short Form–Revised. *Motives for alcohol use* in the past month will be assessed through the 28-item Drinking Motives Questionnaire-Revised [64]. To assess *alcohol use* throughout the intervention period, all groups will be asked to complete the Timeline Followback twice per week [60-62].

##### Anxiety

*Symptoms of social anxiety* will be assessed using the short forms of the Social Interaction Anxiety Scale and the Social Phobia Scale [55]. *Symptoms of depression and anxiety* will be assessed using the 4-item Patient Health Questionnaire-4 [65]. To assess changes in *social anxiety symptoms* throughout the intervention period, all groups will be asked to complete the Social Phobia Weekly Summary Scale [66] biweekly.

##### Covariates and Additional Variables

*Sociodemographic characteristics* will include age, sex, gender, education, employment, country of birth, and primary mental health or substance use concerns. Participants will also be asked about any *psychological and pharmacological treatment* received in the past 3 months (full details given in Multimedia Appendix 1). *Readiness and motivation to change* will be assessed via a readiness ruler (eg, on a scale of 1-10, how ready are you to change your anxiety or drinking) and the University of Rhode Island Change Assessment [72]. The *frequency of other drug use* (cannabis, nonprescribed benzodiazepines, and psychostimulants) will be assessed by the National Institute on Drug Abuse quick screen [73], and *sleep disturbance* over the past month will be assessed using the Pittsburgh Sleep Quality Index [74].

### Intervention and Control Groups

#### Re-train Your Brain ApBM+IBM Intervention Groups

##### Overview

Both the integrated and alternating Re-*t*rain Your Brain interventions contain ApBM and IBM components, delivered in addition to TAU. Participants in both groups will be asked to complete 10 training sessions over a 5-week period. Two sessions will be available to complete each week, and participants will be given 1-week flexibility to complete all the 10 training sessions. Each training session will be of approximately 20 minutes. In addition, as per previous trials [52], before the commencement of the first training session, participants in both intervention groups will receive an online psychoeducational and motivational interviewing–based module, which was adapted from a previous efficacious online program for anxiety and alcohol use [75]. The module provides psychoeducation about anxiety and alcohol use, the interrelationship between these problems, the existence of automatically activated cognitive biases, and the importance of changing these biases. It also explores participants’ reasons for change, and aims to increase intrinsic motivation for (and decrease ambivalence about) change, promotes autonomy and *change talk*, helps participants set goals for what they hope to achieve by completing the training, enhances motivation to train, and harnesses the individual’s capacity for change. The ApBM and IBM components of the integrated and alternating training programs are described later.

##### Alcohol ApBM Component

ApBM is a modified training version of the assessment Alcohol Approach Task, in which participants pull or push a computer mouse in response to the orientation of images (containing alcoholic or nonalcoholic beverages), which zooms the image in or out (Figure 2). For ApBM (unlike the Alcohol Approach Task), 95% of the orientations used to implicitly train avoidance behaviors will contain images of alcoholic beverages, whereas the remaining 5% of frames will contain images of nonalcoholic beverages (and vice versa for orientations used to train approach behaviors). The required push-pull movements are counterbalanced so that half of the participants pull pictures that come in landscape format and push pictures in portrait format, whereas the other half receive the opposite instruction. Participants receive feedback in the form of a green tick or red cross presented on-screen, with a corresponding smiley or sad face emoji. The presentation is repeated if the response is incorrect. To increase motivation, points are awarded for each correct push-pull movement (+1). To familiarize participants with the task requirements, a brief practice round involving five empty rectangular frames in landscape or portrait format will be provided. The alcoholic and nonalcoholic images used in this study were selected to represent the beverage types and brands most commonly consumed by this population, as documented in a recent acceptability study [51].

**Figure 2 figure2:**
[figure not shown]
Example of Approach Bias Modification scenario to illustrate the training procedures.

##### Anxiety IBM Program Component

In IBM training, participants are trained to resolve ambiguous social scenarios with either positive or benign outcomes through the completion of a word fragment (Figure 3) [22]. Each scenario consists of three lines that are ambiguous in terms of valence or emotional interpretation. The participants are instructed to imagine or visualize themselves in each situation described. One word of the story is presented as a word fragment, which disambiguates the story in a positive or benign way. Participants are asked to complete the fragment as quickly as possible by pressing the spacebar when they know what the word is and then to press the key corresponding to the missing letter. The reaction times are recorded. The program continues only when a correct response is provided. After this, a comprehension question appears that reinforces the assigned meaning when the word fragment is completed. Participants answer the question with a *Yes* or *No* response. They subsequently receive feedback (a *correct* or *wrong* answer, with a corresponding smiley or sad face emoji) to reinforce the interpretation imposed by the word fragment. Points are awarded for each correct letter (+1) and correct answer to the comprehension question (+1). The social scenarios are translated versions of those used in previous research [22,45,76], adapted for this study’s target age range of 18-30 years and the Australian context [51]. Three practice trials are given at the outset of the IBM training component.

**Figure 3 figure3:**
[figure not shown]
Example of Interpretation Bias Modification scenario to illustrate the training.

##### Delivery Formats of the Re-train Your Brain ApBM+IBM Intervention

###### Group 1: Integrated ApBM+IBM Intervention, With Biweekly Sessions Combining IBM and ApBM

Group 1 will receive 10 biweekly training sessions containing shortened versions of *both* IBM and ApBM within each session (50:50 ratio) plus TAU. For the ApBM component, participants will be presented with frames containing 10 images of alcoholic beverages and 10 images of nonalcoholic beverages, in a random order. Each alcoholic and nonalcoholic beverage is presented three times, for a total of 60 image presentations. For the IBM component, participants will be presented with three blocks of 10 social scenarios (ie, 30 scenarios per session; 300 across the 10 sessions). Each block will contain eight positive modification (*induction*) scenarios and two probe or irrelevant scenarios that have either a positive or benign outcome, to make the induction less obvious. Blocks are in a fixed order, but the order of the scenarios within blocks is random for each participant.

###### Group 2: Alternating ApBM+IBM Intervention, With Biweekly Sessions Alternating Between IBM and ApBM

Participants in group 2 will receive the same treatment dose as group 1; however, on alternating weeks, participants will receive either ApBM *or* IBM (ie, each session will switch between retraining alcohol or anxiety biases in an alternating pattern; five ApBM and five IBM sessions) plus TAU. For each of the five ApBM training sessions, participants will be presented with 120 (rather than 60) alcoholic and nonalcoholic beverage images (20 alcoholic and 20 nonalcoholic, shown three times in random order), and each of the five IBM sessions will provide 60 scenarios (rather than 30).

#### Control Group (Group 3: TAU Only)

The control group will receive TAU, which will be the model of care provided in accordance with standard practices at their service. The focus of the psychological treatment will not be limited to the provision of treatment for anxiety and/or alcohol use (ie, clients may be receiving treatment for other conditions in addition to anxiety and/or alcohol use). No restrictions will be placed on the type of psychological treatment or how long the client has been receiving the treatment. Details regarding the type, length, and focus of treatment will be ascertained during the baseline and follow-up surveys and reported upon in the trial outcomes (more information given in Multimedia Appendix 1). The decision to have few restrictions tied to the treatment offered as part of TAU follows a desire to test the CBM program in the context of real-world care and to evaluate the adjunctive intervention with a deployment focus. This group will be offered the opportunity to receive the *Re-train Your Brain* program (in whichever format is deemed preferable by participants) after all follow-up surveys and measurements are taken at the 3-month assessment point.

### Procedure

#### Study Procedure

All participants will be directed to the *Re-train Your Brain* website, which contains detailed information about the study and provides a direct link to the online participant information statement and consent form. After providing consent, prospective participants will complete a brief, 10-minute online screening survey to determine eligibility. Eligible participants will gain access to an online baseline survey, which will take approximately 30 minutes to complete. Participants will be asked to provide their name, email, and postal address so that the research team may post them a computer mouse to complete a cognitive assessment (*note*: as these assessments are reaction time based, this will ensure consistency in mouse settings between participants, such as pointer speed, etc) and send them a link to the alcohol approach and interpretation bias cognitive assessment. Immediately following the cognitive assessment, participants will be individually randomized by the study website to receive the following: (1) the *integrated Re-train Your Brain* intervention plus TAU (n=30), (2) the *alternating Re-train Your Brain* intervention TAU (n=30), or (3) TAU only (n=30). Participants in the *Re-train Your Brain* intervention groups will be asked to complete a 30-minute motivational interviewing or psychoeducation-based module, followed by 10 cognitive training sessions, delivered online twice per week for 5 weeks (approximately 2-4 days apart). Participants will be reminded of these training sessions via multiple reminder calls, emails, and SMS text messages. As difficulty and boredom are intrinsically part of these kinds of implicit interventions, participants will also receive 3-4 brief motivational enhancement texts or emails over the 5-week program to normalize any difficulties encountered in the training execution and reaffirm their commitment to change. In addition, to maximize engagement with the research trial, participants in all groups will be asked to complete two weekly 5-minute assessments of their anxiety and alcohol use symptoms, for which they will receive a Aus $5 (US $3.80) e-gift voucher per occasion (10 total), with an accumulated voucher (max Aus $50; US $37.70) paid at the end of the treatment period.

All participants will be emailed a link to complete an online survey and a (separate) cognitive assessment at postintervention (ie, 6 weeks postbaseline, to provide 1 week of flexibility in the rate of training completion) and 3 months postbaseline. The survey and cognitive assessments are expected to take approximately 45-60 minutes (combined) to complete at each time point. Consistent with previous online trials [77,78], participants who complete both the online survey and cognitive assessment will receive an Aus $30 (US $22.60) e-gift voucher at each time point as reimbursement for their time participating in the research. To minimize data attrition, the following evidence-based strategies will be used [79,80]: (1) monetary incentives for each assessment completed, (2) collection of multiple sources of contact information (eg, email, mobile number, and postal address), (3) user-friendly electronic survey design that can be completed via multiple devices (eg, via mobile phone), (4) personalized reminder messages (SMS text messaging and email) to complete surveys or cognitive assessments, and (5) a follow-up letter and telephone call to those participants who do not respond. The intervention and cognitive assessments will be accessed via the study website and run using JavaScript, whereas all online surveys will be delivered via Qualtrics. The trial will be conducted in accordance with the SPIRIT (Standard Protocol Items: Recommendations for Interventional Trials) 2013 Statement and CONSORT (Consolidated Standards of Reporting Trials) guidelines.

#### Randomization

To avoid bias, participants will be individually randomized to the *Re-train Your Brain* integrated group, the *Re-train Your Brain* alternating group, or the control group (on a 1:1:1: basis) via the trial website using a computer-generated randomization sequence, which is concealed from the investigators. This process removes the potential for researcher involvement. Randomization will occur directly after the completion of the online baseline cognitive assessment (Figure 1).

### Statistical Analysis and Power Calculations

As this is a pilot trial, a formal power calculation is not required [81,82]. The pilot trial is essential to determine the expected size of effect, which will be used to inform the sample size of a future definitive RCT aiming to assess the efficacy of the *Re-train Your Brain* program. Rates of attrition will be used to indicate estimated follow-up rates in future trials. On the basis of several rules of thumb used to determine an appropriate sample size for a pilot study [83-85], a sample size of 90 young people (30 per arm) was selected to provide sufficient data on the feasibility, acceptability, and preliminary efficacy of the program, although we recognize that the scope of this pilot trial does not allow for a fully powered test of efficacy. Data will be collated and analyzed using StataCorp data analysis software [86].

Descriptive statistics for primary and secondary outcomes will be conducted based on frequencies and cross-tabulations. Analyses for secondary (preliminary) efficacy outcomes will use multilevel mixed effects analysis for repeated measures, which is a flexible analytic approach for modeling change over time using RCT data [87,88]. All models will use baseline measurements as the reference point to estimate participant-specific starting points and change over time. The intervention condition will be represented by a dummy-coded variable, and the condition by time interaction will be examined to assess between-group differences in outcomes over time. Analyses will be consistent with an intention-to-treat framework, with all randomized participants included in the analysis models, regardless of training completion or loss to follow-up. Missing data will be accommodated in these models using maximum likelihood estimation. Preliminary models will be estimated, with model fit statistics examined to determine the most appropriate model and covariance structure. Cohen *d* will be calculated from model-estimated marginal means and SEs to determine the size of the effect between conditions at the relevant end point. In addition, effect sizes will be analyzed as a function of session completion (ie, completion of six or more training sessions, given that this has been identified as the mean optimum number of ApBM sessions in past research [67]).

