One of the main strengths of this study is also its main limitation: that is, its web-based delivery. First, internet interventions are conducted in a less-controlled home environment that may pose several online distractions (eg, email notifications) and offline distractions (eg, housemates or phone calls), which have the potential to impact the study results. Second, web-based interventions also have higher rates of attrition compared with standard face-to-face treatments (eg, 34.2% vs 24.6%, respectively) [90]. Further increasing the risk of attrition, CBM interventions are inherently repetitive and as such are sometimes considered boring because of the monotonous nature of the tasks [28,91]. To help overcome these limitations, at the start of each session, participants are reminded of the importance of conducting training in a quiet environment where they can concentrate for a 20-minute block. To leverage on participants’ intrinsic motivation for change and maximize their initial buy-in, a compelling rationale and motivational enhancement module is provided at the outset of the program. These components will set expectations about the purpose and nature of the intervention (eg, computerized and repetitive training), which will likely enhance motivation to train and, thus, result in increased adherence and lower attrition. In addition, multiple evidence-based strategies to minimize treatment and study attrition will be used, such as monetary incentives, email and SMS text messaging reminders, and explanation of the importance of completing the sessions and follow-up surveys to participants [79,80]. Taken together, the possible threats presented by the web-based delivery of the intervention are outweighed by the possibilities and benefits it may offer.

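### If maximum likelihood here means full ML with normal-based inference, intervals for continuous secondary outcomes run about 3% to 5% too narrow at this sample size

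*Protocol article*

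**What the plan says.** All the relevant wording on method is in the Protocol article, Statistical Analysis and Power Calculations.

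- **Size.** The article states that "a sample size of 90 young people (30 per arm) was selected", based on rules of thumb; "As this is a pilot trial, a formal power calculation is not required".
- **Estimation.** Secondary outcomes are analysed with multilevel mixed-effects models for repeated measures, including a condition-by-time interaction. On missing data: "Missing data will be accommodated in these models using maximum likelihood estimation".
- **Covariance.** "Preliminary models will be estimated, with model fit statistics examined to determine the most appropriate model and covariance structure". No candidate structures, criterion or fallback are listed.
- **Analysis set.** Intention to treat, "with all randomized participants included in the analysis models, regardless of training completion or loss to follow-up".
- **Reporting.** Cohen d is taken from model-estimated marginal means and their standard errors. The section says that the pilot is to determine the expected effect size for sizing a definitive trial. It mentions no confidence level, test, reference distribution or degrees-of-freedom method.

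The article gives no expected dropout for this trial. The only figures are general ones, under Strengths and Limitations: web-based against face-to-face attrition ("eg, 34.2% vs 24.6%, respectively").

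**The concern.** Full maximum likelihood divides residual variation by the number of observations and makes no allowance for the arm-by-time means that are also estimated. In a large trial this does not matter. With about 20 to 30 people per arm it makes standard errors visibly too small, and a normal quantile in place of a t quantile shortens the interval again. REML with small-sample degrees of freedom removes both problems. It uses the same observed data and the same missing-at-random assumption.

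Two things are at stake. The intervals around the condition-by-time effects would look slightly more precise than they are. And if the standard deviation behind Cohen d is recovered from ML standard errors, d is slightly too large, and d is what the pilot is meant to pass on to the definitive trial.

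**Working it through.** **Inputs from the article.** 90 randomised, 30 in each of 3 arms; assessments at baseline, 6 weeks and 3 months; background attrition of 24.6% and 34.2%.

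**Assumptions, not in the article.** Full ML; normal quantiles; two-sided 5%; normally distributed outcomes; dropout completely at random.

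The plan states no interval width or error rate to reproduce. Its sample size is internally consistent: 3 × 30 = 90.

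**Completers.** At 34.2% loss, 90 × 0.658 = 59.2, taken as 59 (30 × 0.658 = 19.7 per arm). At 24.6% loss, 30 × 0.754 = 22.6 per arm, rounded to 23, so 69.

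**Closed form.** At one follow-up with p = 3 arm means and n completers, the width of an ML interval with a normal quantile, relative to a REML interval with a t quantile, is

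ratio = √((n − p)/n) × z(0.975) / t(0.975, n − p).

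The type I error of the ML test is 2 × P(t with n − p df > 1.96 × √((n − p)/n)). The inflation of d from the divisor alone is √(n/(n − p)) − 1.

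| n | SE factor | z/t | Width ratio | Too narrow by | Type I error | d inflated by |
|---|---|---|---|---|---|---|
| 90 (no loss) | √(87/90) = 0.983 | 1.960/1.988 = 0.986 | 0.970 | 3.0% | 5.7% | 1.7% |
| 69 (24.6% lost) | √(66/69) = 0.978 | 1.960/1.997 = 0.982 | 0.960 | 4.0% | 6.0% | 2.3% |
| 59 (34.2% lost) | √(56/59) = 0.974 | 1.960/2.003 = 0.978 | 0.953 | 4.7% | 6.1% | 2.6% |

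This treats one follow-up as a cross-section of completers. The planned model also keeps the baseline data of dropouts, so it was checked by simulation.

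**Simulation.** 3 × 30 participants, three times, saturated arm-by-time means, within-person correlations 0.5 to 0.7, random monotone dropout reaching 34.2%. There were four covariance and dropout scenarios and two follow-up times, so eight cells of 1,600 runs. The Monte Carlo standard error per cell is √(0.95 × 0.05/1600) = 0.5 points.

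| Method | Mean coverage of 95% interval | Width relative to REML |
|---|---|---|
| ML, covariance chosen by AIC, normal quantile | 94.3% (cells 93.7% to 95.4%) | 0.948 to 0.975 |
| ML, unstructured fixed in advance, normal quantile | 94.2% | 0.954 to 0.962 |
| REML, unstructured, Satterthwaite t | 95.3% (cells 94.6% to 96.4%) | 1 |

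The first two rows separate the causes. With the covariance fixed and no selection at all, ML is already about 4% to 4.5% narrower. Selection by AIC moves the width by at most about 1 point in the narrowing direction. In some cells it leaves a relatively wider interval, and average coverage is essentially unchanged.

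A second simulation, with a further 10% assumed lost by 3 months, tested integrated against TAU at 6 weeks in four covariance scenarios. Type I error was 7.0%, 6.9%, 7.0% and 5.9% for fit-chosen ML with normal tests, against 6.0%, 5.3%, 5.7% and 4.8% for REML with Satterthwaite t. The gain is 1.0 to 1.6 points (Monte Carlo standard error of each rate 0.36 points).

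**Scale of the effect on d.** At 59 completers a true d of 0.50 (illustrative) would be reported as about 0.50 × 1.026 = 0.513. A sample size taken straight from that d would be 56/59 = 0.95 of the correct one, about 5% too small. For comparison, the sampling standard error of d at 20 per arm is about √(2/20) = 0.32.

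**The case against.** The strongest reply is that the article does not commit to the method criticised. The sentence on maximum likelihood explains how missing data are handled; REML is also a likelihood method that uses all observed data. The choice of variant and of degrees of freedom is commonly left to a statistical analysis plan, and none is shown. **This stands as a limit:** the size given here is conditional. It does not remove the point, because the estimator and the data-driven choice of covariance are both stated, and full ML is the plain reading.

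Several stronger readings are tempting, and the documents do not support them:

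- **That about 20 completers per arm is planned.** It follows only from a general web-attrition rate. The article describes retention measures and keeps all 90 in the models. Some narrowing remains without any loss, but it is then 3%.
- **That selection by fit causes the problem.** The simulation does not show this. A random-intercept model retained while the SD grows by half does badly (12% too narrow, type I error 9.1%), but a check of fit could detect that failure.
- **That the error is always optimistic.** One of the eight cells for fit-chosen ML covered above 95%.
- **That no comparison of structures is ever needed.** Six covariance parameters suffice for three assessments. The twice-weekly in-treatment measures have up to 10 occasions, which would need 10 × 11/2 = 55.
- **That the analysis by completion of six or more sessions is badly distorted.** The article gives neither the size of that group nor a separate model for it.

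It is also fair to say that efficacy is secondary, declared not fully powered, and tied to no decision rule, and that the bias in d is small beside its sampling error.

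**Conclusion.** The point holds as a minor one. With full ML and normal-based inference, intervals for condition-by-time effects on continuous secondary outcomes are about 3% too narrow with complete follow-up and 4% to 5% too narrow at 24.6% to 34.2% attrition. Type I error is about 6% in closed form, and Cohen d is inflated by about 2% to 3% if it is derived from those standard errors. The ML divisor and the missing t correction account for this.

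The conclusion rests on full ML, normal quantiles, two-sided 5%, normal outcomes and random dropout, none of which the article states. If the models are in fact fitted by REML with small-sample degrees of freedom, only the wording and the open choice of covariance remain. Count outcomes such as binge-drinking days lie outside these calculations. The primary feasibility and acceptability results are descriptive and unaffected.

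**What to change.** For each continuous outcome measured at baseline, 6 weeks and 3 months, state one model in advance: arm by categorical time, unstructured covariance over the three assessments, fitted by REML with Kenward-Roger or Satterthwaite degrees of freedom. Name one simpler structure to be used only if that model fails to converge. Comparison of structures by fit can stay for the twice-weekly in-treatment measures, preferably with the candidates and criterion listed. Count outcomes need their own model and are not covered by this change.

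Cost: a sentence in the plan and two software settings. The sample stays at 90, every randomised participant stays in the model, and the missing-data assumption does not change. The price is intervals about 3% to 5% wider.
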